### Data management

The project is dedicated to upholding the anonymity and confidentiality of participants throughout all stages, encompassing screening, recruitment, testing, evaluation, and dissemination procedures. Data collection, usage, and storage strictly adhere to national laws, the General Data Protection Regulation (GDPR) of EU, and APPI. Participants retain rights, such as access, information, withdrawal, and data erasure. Additionally, servers are situated in the European Union and comply with the GDPR standards. Data collection follows the principle of data minimization, ensuring that personal information collected is directly relevant and necessary for the specific goals of testing and evaluation. Specific software with blocks and data entry checks is employed to minimize entry errors. All screening data are discarded upon project completion. During testing procedures, any visual, auditory, and sensory data processed by the robot are discarded after completing the procedures, except for the number of interactions logged with each participant, which remains anonymous. After the conclusion of this project, all research data will be openly available for secondary analysis after 3 years.

### Data analysis

A comprehensive analysis plan will be established to serve as the foundation for conducting subsequent analyses. This plan will outline the methodologies, procedures, and criteria for conducting the analyses, ensuring a systematic and well-organized approach to data interpretation and result generation.

#### Data collected by the researchers

The first step of the data analysis will deal with the description of the sample. Continuous variables will be reported as either mean and standard deviation or median and interquartile range based on their distribution (assessed using the Kolmogorov–Smirnov test). Categorical variables will be expressed as an absolute number and percentage. Comparison of baseline measurements between groups will be evaluated by unpaired t-test (for normal distribution), Mann–Whitney U tests (for non-normal distribution), or chi-square tests (for categorical variables). Within each group, independent and dependent variables will be compared between the pre-conditions and post-conditions using the same tests as appropriate. The treatment effect on the outcome variables will be evaluated by using repeated measures ANOVA, in order to compare the changes over time in the outcome measures between the intervention group and control group. Moreover, a linear regression model on the outcome variation between baseline and follow-up will be estimated in order to evaluate the effect of the treatment adjusted for all potential confounders. For the analysis of the results, the two types of subjects, stratified according to the MoCA cutoff (score ≥ 26 for cognitively healthy subjects, score 22 to 25 for subjects with mild cognitive decline), will be considered separately. Descriptive statistical analyses will be performed on the quantitative data with SPSS or R studio.

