#### Sample size determination

In the study by Summers et al. (42), the EuroQol 5 dimensions (EQ 5D) was evaluated in two groups of older adults with physical pre-frailty conditions. EQ 5D, a test widely used to measure health status-related quality of life, was used to calculate the sample size. Assuming an overall sample size of 220 subjects (110 cases and 110 controls), 2 repeated assessments (baseline and follow-up), a significance level of 0.05, power of 90%, a correlation among repeated measures of 0.5, and a non-sphericity correction ε of 1 in an ANOVA model within-between interactions, the achieved effect size for this study is 11% (corresponding to a small effect size in a coherent way with the literature). Even factoring in a dropout rate of 10%, the total number needed would be 240 subjects, evenly divided into 120 cases and 120 controls. The hypothesis is that this sample size is more than adequate to detect variations in secondary outcomes. For these secondary outcomes, a treatment effect size is assumed to be similar to or even greater than the one identified for the primary outcome.

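### Within-group pre/post comparisons are assigned independent-samples tests although the data are paired; the resulting p-values are too large, in supporting analyses only

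*Protocol article*

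**What the plan says.** The relevant text is in the protocol article, Data analysis, under Data collected by the researchers. For the baseline comparison it states: "Comparison of baseline measurements between groups will be evaluated by unpaired t-test (for normal distribution), Mann–Whitney U tests (for non-normal distribution), or chi-square tests". The last of these is meant for categorical data. The next sentence reads: "Within each group, independent and dependent variables will be compared between the pre-conditions and post-conditions using the same tests as appropriate". The only tests this can refer back to are the three just listed. The paired t-test, the Wilcoxon signed-rank test and the McNemar test appear nowhere in the article.

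The treatment effect is handled separately: "The treatment effect on the outcome variables will be evaluated by using repeated measures ANOVA, in order to compare the changes over time" between the two groups. A linear regression on the change from baseline to follow-up, adjusted for confounders, is added.

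The Sample size determination section treats the two assessments as correlated, with "a correlation among repeated measures of 0.5". Table 3 confirms that the same people are measured more than once. EQ-5D-5L, eHEALS and the short FFQ are taken at T0 and T2, and the UCLA scale at T0, T1 and T2. MoCA, GDS and SPPB are taken at recruitment and T2.

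**The concern.** An independent-samples test computes the variance of a difference as if the two sets of values came from different people. When each person supplies both values and these are positively correlated, the change varies less than the test assumes. The p-value then no longer has its nominal meaning.

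The article therefore assumes correlated assessments when it sizes the trial and names tests that ignore the correlation when it describes within-group change. This is a stated method rather than a detail left for later, so an analysis plan that copies the sentence would carry the error into every within-group comparison. At stake are real within-group changes that would be reported as non-significant. The primary conclusion of the trial is not at stake.

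**Working it through.** **Inputs from the Sample size determination section.** Numbers and assessments: "Assuming an overall sample size of 220 subjects (110 cases and 110 controls), 2 repeated assessments (baseline and follow-up"). Test level and target power: "a significance level of 0.05, power of 90" per cent. Link between a participant's two values: "a correlation among repeated measures of 0.5". The sphericity correction is set to 1. The stated result is "the achieved effect size for this study is 11" per cent, read here as Cohen's f = 0.11. The correlations 0.3 and 0.7 used below are my assumed range around the planning value.

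**Step 1: the plan's own figure.** For the within-between interaction with N = 220 and m = 2 assessments, the noncentrality is λ = f²·N·m/(1 − ρ) = 0.11² × 220 × 2/0.5 = 10.65, with 1 and 218 degrees of freedom. Power is 0.901, and f for exactly 90% power is 0.1098. The stated figure reproduces, and it depends on the correlation of 0.5.

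**Step 2: variance of the mean change within one arm.** For n participants with standard deviation σ at each assessment:

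- true variance: 2σ²(1 − ρ)/n
- variance assumed by the unpaired t-test: 2σ²/n
- ratio of assumed to true standard error: 1/√(1 − ρ), which at ρ = 0.5 is 1/√0.5 = 1.41

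**Step 3: true type I error of the unpaired t-test.** The test rejects at its own critical value t* on 2n − 2 degrees of freedom. On the correct scale this equals t*/√(1 − ρ), so the true type I error is 2·P(t with n − 1 df > t*/√(1 − ρ)).

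**Step 4: power.** Take the change d (in SD units) that the paired t-test detects with 90% power. With noncentrality d√n/√(2(1 − ρ)), find the probability of exceeding the larger threshold from Step 3. At ρ = 0.5, d = 0.312 and the noncentrality is 0.312 × √110/√1 = 3.27.

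Results for n = 110 per arm:

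| ρ | SE ratio | True type I error (nominal 5%) | d detected by paired t with 90% power | Power of unpaired t for the same d |
|---|---|---|---|---|
| 0.3 (assumed) | 1.20 | 2.0% | 0.369 SD | 82% |
| 0.5 (planning value) | 1.41 | 0.63% | 0.312 SD | about 68% |
| 0.7 (assumed) | 1.83 | 0.05% | 0.242 SD | 38% |

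With 120 per arm the results are almost the same (0.62% at ρ = 0.5).

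**Step 5: simulation check.** Normal data with no change, n = 110, ρ = 0.5; 40,000 runs for the t-tests and 5,000 for the others. The chi-square and McNemar tests were run on the same data cut into two categories.

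| Test named in the article | Rejection rate | Paired counterpart | Rejection rate |
|---|---|---|---|
| Unpaired t | 0.006 | Paired t | 0.051 |
| Mann–Whitney U | 0.005 | Wilcoxon signed-rank | 0.054 |
| Chi-square | 0.018 | McNemar | 0.051 |

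The paired tests hold close to the nominal level. The three named tests fall well below it, the chi-square test less far than the other two.

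**The case against.** The strongest reply is that the sentence is loosely worded rather than wrong. Its closing qualifier might be meant to admit the paired version of each test. The authors clearly know that the data are correlated, and the article promises a comprehensive analysis plan. This reading is possible, but it is the less natural one: the preceding list is keyed to normal, non-normal and categorical data, so the qualifier most readily means choosing among those three tests. A later plan could correct the sentence, but the sentence as it stands does not name a valid test.

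The second reply concerns consequences, and it stands. The treatment effect is assigned to the repeated measures ANOVA and the change regression. Both use each participant's own pre and post values, and the sample size rests on the interaction term. With positive correlation the error also makes false positives rarer.

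A reader might infer more than the documents support:

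- **Significance in one arm only will be read as efficacy.** The article does not say this; it assigns efficacy to the between-group analyses. Such a misreading would be just as possible with correct paired tests.
- **Regression to the mean affects MoCA, GDS and SPPB, which also serve as entry criteria.** Unpaired tests do not cause this and paired tests do not cure it. It is a matter for the randomised comparison, which is already planned.
- **Confidence intervals will be too wide.** No intervals are planned for these comparisons. The point would apply only if they were reported.

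**Conclusion.** The point holds, at minor to moderate severity. As written, the article assigns independent-samples tests to paired data, contrary to its own design assumption. At the planning correlation the unpaired t-test runs at about 0.6% instead of 5%, and power falls from 90% to about 68%.

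These sizes rest on 110 participants per arm, equal variances at the two assessments and a positive correlation. The value 0.5 is the article's planning figure for EQ-5D. Other outcomes may differ, which is why a range is shown. The standard-error ratio applies to the t-test only; the rank and chi-square figures come from the simulation.

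It would be tempting to conclude that the efficacy analysis is invalid or that false-positive findings are inflated. Neither follows: the error is conservative and confined to supporting comparisons.

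**What to change.** In Data collected by the researchers, replace the reference back to the baseline tests with named paired methods: paired t-test, Wilcoxon signed-rank test, or McNemar test (marginal homogeneity test for more than two categories), according to variable type and distribution. Add that within-group results are descriptive and that conclusions on the treatment effect rest on the between-group analysis.

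The cost is one or two sentences in the analysis section, carried into the statistical analysis plan. Data collection, sample size and the treatment-effect models do not change.

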### Outcome measures

All outcomes will be measured following a standardized operating procedure. The primary endpoint of the study is constituted by the improvement in the quality of life after the use of the e-VITA system, to be measured through the EQ-5D-5L, after 6 months of training.

The secondary endpoints encompass: (1) adherence to the coaching intervention, measured by the frequency of technological device usage, and collected through semi-structured interviews and technical data; (2) usability and the user experience of the overall system assessed using the System Usability Scale (SUS) (62) at both the midpoint and the conclusion of the experiments, along with the User Experience Questionnaire [UEQ (63) and UEQ+ (64)] in the middle and at the end of the experiments; (3) improvement in eHealth literacy, to be addressed through the eHealth Literacy Scale (eHEALS) (65), social connectedness through the UCLA Loneliness scale (UCLA) (66), nutritional state through the short version of Food Frequency Questionnaire (FFQ) (67) to estimate the frequency of daily food intake over a period, cognitive status, through Montreal Cognitive Assessment (MoCA) (39), psychological mood through the Geriatric Depression Scale (GDS) (40), functional status through Short Physical Performce Battery (SPPB) (41), participation to leisure activities through an *ad-hoc* checklist; meets the participant’s objectives through ADTPA-5 (scale B and E adapted) (68). A semi-structured interview will be used to complement the information collected by questionnaires, focusing on acceptability, attitude, usability, and cost–benefit analysis; other questionnaires will be used to better understand our participants’ sociodemographics questionnaire, Clinical Frailty Scale (CFS) (38), Big Five Inventory – 10 (BFI-10) (69), and Affinity for Technology Interaction (ATI) (70).

Table 3 presents a concise overview of all collected data and their respective collection time points.

**Table 3 tab3:** Schedule of assessment and outcome measures.

Dimension	Scale	R	T0	T1	T2
Clinical frailty scale	CFS	X			
Cognitive status	MoCA	X			X
Psychological status	GDS	X			X
Physical capacity	SPPB	X			X
Overall health status	Clinical anamnesis	X			
General information	Socio-demographics questionnaire	X			
Quality of life	EQ-5D-5L		X		X
Goals and expectation	ATDPA-5 (Scale B and E)		X		X (Scale B)
eHealth literacy	eHEALS		X		X
Social connectedness	UCLA		X	X	X
Personality	Big Five Inventory – 10 items		X		

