Nutrition	Short FFQ		X		X
Adherence	Collected through the system and interview			X	X
Leisure activities	Physical and leisure activity checklist		X	X	X
Usability	SUS			X	X
User experience	UEQ, UEQ+			X	X
Attitude, usability, acceptability and cost–benefit analysis	Semi-structured interview				X
Affinity for technology interaction	ATI		X		

R, recruitment; T0, first evaluation; T1, intermediate evaluation; T2, final evaluation; CFS, Clinical Frailty Scale; MoCA, Montreal Cognitive Assessment; GDS, Geriatric Depression Scale; SPPB, Short Physical Performance Battery; ATDPA, Assistive Technology Device Predisposition Assessment; FFQ, Food frequency questionnaires; SUS, System Usability Scale; UEQ, User Experience Questionnaire; ATI, Affinity for Technology Interaction.

The scales which will be used during the evaluations are described below.

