### Risk–benefit analysis

During the use of robotic platforms or, in wider terms of technological applications, a general difficulty in distinguishing between the artificial world and reality may occur. Especially, in the case of vulnerable older adults, the interaction may generate a general feeling of attachment and dependency. To avoid this, e-VITA has been designed to not look like a human but to preserve artificial aesthetics, as suggested by the guidelines. In addition, during the first contact with the participants but also during all the interventions, researchers will be in contact with the users, continuously stimulating awareness about the technological applications and monitoring the appropriateness of the use of the solution in terms of autonomy of the users, specific needs, and personal preferences. In particular, following the recommendations provided by Comitato nazionale di bioetica (Cnb) of the Ministry of Health (71) on robotics and roboethics, the exit strategy of e-VITA will aim to:

promote adequate experimentation of robotics in the field assistance in order to ensure conditions for the physical and psychological integrity of the user, explaining the risks and benefits, which was highlighted also in the informed consent;ensure both equitable access to robotic and general technologies and the use of robots to assist and not to replace humans, in order to avoid delegating the irreplaceable human task of care and assistance to the machine;the need that the introduction of robotics in medicine entails always the real consideration of the benefits, of the complexity of the change complete with the structure of the services and the economic burden that this entails.

There is a risk that the older adults may wish to stop interacting with the technological devices (for example, because they do not like the NAO robot). In this case, the experiment will be immediately stopped and terminated.

The presence and use of technological devices (virtual coaches and sensors) in participants’ homes can be a source of discomfort. Therefore, pre-studies with end-users (older adults) and stakeholders (informal carers, health professionals, family, NGOs etc.) have been carried out in order to propose virtual coaches that meet the needs of older adults. In addition, safety procedures were also designed to limit the risks as much as possible.

To protect the safety of participants:

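### For loneliness (and the leisure checklist, if it is given a summary score), the named analyses cannot use the 3-month value of a participant without a 6-month value; a likelihood mixed model can, at almost no cost

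*Protocol article*

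**What the plan says.** Under Data analysis (Data collected by the researchers), the protocol article names one method for all outcomes: "The treatment effect on the outcome variables will be evaluated by using repeated measures ANOVA". It adds a covariate-adjusted analysis: "a linear regression model on the outcome variation between baseline and follow-up will be estimated".

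Table 3 under Outcome measures gives two repeated scales a baseline and both later visits: "Social connectedness UCLA X X X" and "Physical and leisure activity checklist X X X". The EQ-5D-5L is scheduled at T0 and T2 only. The SUS, UEQ and adherence are collected at T1 and T2 and have no baseline.

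On loss, Sample size determination allows for 10% ("Even factoring in a dropout rate of 10" per cent). Risk–benefit analysis foresees that a participant may wish to stop using the devices, for example from dislike of a robot, and says: "In this case, the experiment will be immediately stopped and terminated". The article mentions no mixed model or imputation. It says that a comprehensive analysis plan will be established.

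**The concern.** Classical repeated-measures ANOVA needs a complete set of the visits it analyses. With three visits and no imputation, a participant with T0 and T1 but no T2 is left out, and so is one with T0 and T2 but no T1. The regression on change needs T0 and T2, so it recovers the second kind of participant but not the first.

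The T1 value shows how a later dropout was doing at 3 months. If that value is related to leaving, and more so in the device arm, then completers are a selected group and the contrast between arms at T2 is distorted. The distortion would favour e-VITA if the people who leave are those not improving. Loneliness is the scale closest to the trial's aim of reducing social exclusion, so it is worth protecting even as a secondary outcome.

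**Working it through.** **The plan's own figure.** Inputs from Sample size determination: f = 0.11, N = 220, m = 2 assessments, correlation 0.5, alpha 0.05. The noncentrality is f² × N × m / (1 − ρ) = 0.0121 × 220 × 2 / 0.5 = 10.648. With 1 and 218 degrees of freedom the power is 0.901, so the stated 90% reproduces. With 240 enrolled and 10% lost, 240 × 0.90 = 216 have both T0 and T2.

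**Who is analysed under random loss.** Assumptions: 120 per arm, 5% lost before T1, 5% lost between T1 and T2, and 5% of completers missing T1 only.
- Per arm: 6 with T0 only, 6 with T0 and T1, 108 × 0.05 = 5.4 with T0 and T2, and 102.6 with all three.
- Three-visit listwise ANOVA: 240 × 0.90 × 0.95 = 205.
- Change-score regression: 240 × 0.90 = 216.
- Mixed model: all 240 contribute what they have.

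**Variance of the arm difference in T2 − T0 change** (SD 1). Each complete-case variance is 2 × 2(1 − ρ02) / n per arm. The mixed-model variance comes from summing the inverse covariance matrices over the four visit patterns, inverting the sum, applying the contrast (−1, 0, 1), and doubling for two arms.

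| Correlations T0–T1 / T1–T2 / T0–T2 | Listwise (n = 102.6) | Change score (n = 108) | Mixed model | Ratios to mixed model |
|---|---|---|---|---|
| 0.5 / 0.5 / 0.5 | 2 / 102.6 = 0.01949 | 2 / 108 = 0.01852 | 0.01797 | 1.08 and 1.03 |
| 0.7 / 0.7 / 0.6 | 1.6 / 102.6 = 0.01559 | 1.6 / 108 = 0.01481 | 0.01437 | 1.09 and 1.03 |

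The excess variance is about 8% for the listwise ANOVA and about 3% for the change score. There is no bias under random loss.

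**Bias if leaving depends on T1** (simulation; no true effect, 120 per arm, SD 1, the same two correlation sets, 1,500 runs per setting). Device-arm loss after T1 is logistic in the T1 − T0 change, with slope 1.0 or 1.5. Control loss is random. The test is the complete-case T2 − T0 contrast.

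| Loss, device / control | Bias towards e-VITA (SD) | Two-sided type I error |
|---|---|---|
| about 8–10% / 10% | 0.033 to 0.062 | 6.1% to 7.5% |
| about 17–20% / 5% | 0.063 to 0.111 | 8.1% to 12.4% |

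The mixed model's bias was at most 0.004 SD. For scale, the standard error of the contrast with 108 per arm at correlation 0.5 is √(2/108) = 0.136 SD. A bias of 0.03 to 0.06 SD is therefore 0.03/0.136 = 0.22 to 0.06/0.136 = 0.44 of a standard error.

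**The omnibus three-visit group-by-time F test** (separate simulation, correlation 0.5, 2,000 runs). Each range runs from weak selection (slope 1) to strict selection on T1 change. The test is hit harder than the T2 contrast because selection also distorts the T1 means among completers.
- Loss 10% / 10%: bias 0.04 to 0.10 SD, type I error 7% to 23%.
- Loss 15% / 5%: bias 0.06 to 0.13 SD, type I error 13% to 46%.
- Loss 20% / 0%: bias 0.09 to 0.18 SD, type I error 21% to 69%.

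**Limit of the remedy.** If leaving depends on the unseen T2 value (15% / 5%, slope 2, no true effect), complete-case bias is 0.20 SD and mixed-model bias is still 0.14 SD.

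**The case against.** The strongest reply is that the article sets no deletion rule. It promises a fuller analysis plan, handling of missing data commonly belongs there, and a repeated-measures ANOVA can be run on imputed data. A reader might infer that the protocol prescribes listwise deletion. It does not, and the point holds only where no imputation is added. What remains is that the article has already named the method for these outcomes, and a better-suited one exists.

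A reader might also infer that anyone who misses a visit is lost from every analysis. That goes too far. The text does not say that all three visits enter the ANOVA: the sample size uses two assessments, and the regression uses baseline and follow-up. A participant who misses only T1 stays in the regression, which removes most of the precision loss (3% against 8%).

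Nor do the documents show that non-improving device users will leave after T1. The example given for stopping is dislike of the device, with no timing and no link to loneliness, and the article plans monitoring to prevent dropout. The bias figures are conditional on an assumed mechanism. The highest ones need strict selection with all loss in one arm.

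Two further limits stand. The leisure checklist is an ad-hoc set of Likert questions with a section for personal practices and no stated total score, so UCLA is the one clear case. The mixed model is unbiased only under missing at random.

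**Conclusion.** The point holds as a cheap improvement to a stated method. It is not a demonstrated bias in the trial. For UCLA loneliness, and for the leisure checklist if a summary score is defined, neither named analysis can use the T1 value of a participant without T2 unless imputation is added. If loss is random, the price is about 3% to 8% in variance. If device-arm loss depends on poor T1 change, the complete-case T2 contrast leans towards e-VITA by about 0.03 to 0.06 SD at around 10% loss, with type I error of about 6 to 7%, and by more when loss is larger or more unequal.

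These sizes rest on assumed correlations, an SD of 1, an assumed split of loss by arm and an assumed selection pattern; the article gives only the overall 10%. A reader might extend the point to the primary outcome, but the EQ-5D-5L has no T1 value to recover.

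**What to change.** Under Data collected by the researchers, for outcomes measured at T0, T1 and T2, replace repeated-measures ANOVA with a linear mixed model fitted by REML. Use an unstructured within-person covariance and fixed effects for visit, arm and arm-by-visit, on all available assessments of all randomised participants. Report the arm difference in change at T2 with its 95% confidence interval. State the missing-at-random assumption, and say that the model reduces but does not remove bias if loss depends on unseen values. Define a summary score for the leisure checklist before applying the model to it. Keep the complete-case ANOVA as a sensitivity analysis at most.

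The cost is a few sentences and a few lines of code. SPSS and R, which the article names for descriptive work, both fit this model. No extra visits or data are needed. The downside is reliance on missing at random.

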### Design/methodology

#### Recruitment

Patients are selected by the Neurology Operating Unit and Rehabilitation Medicine Operating Unit of IRCCS INRCA in the Ancona branch. After a reflection period of 2 weeks followed by reading the information letter and the consent form received by email, the participants who confirmed their wish to participate in the research by writing or orally will be invited by the investigator to consult a doctor during 3 months, preceding the start of the research. The doctor, volunteering to carry out the inclusion visits, will be the first to give the participants an information letter and two consent forms. Once the consent forms have undergone thorough proofreading and received signatures from both the participant and the doctor, the doctor will assess the participant’s eligibility for the research using an anamnesis Clinical Frailty Scale (CFS) (38), Montreal Cognitive Assessment (MOCA) (39), Geriatric Depression Scale (GDS) (40), and Short Physical Performance Battery (SPPB) (41). This comprehensive medical examination, conducted before the commencement of the experiment, will determine whether participants meet the inclusion criteria. Those who have signed the consent form but do not meet the inclusion criteria as confirmed by the doctor will be excluded from the research. The trial is scheduled to commence in May 2023 and is anticipated to conclude in December 2023.

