#### Participants

Each European country will enroll 40 subjects.

The inclusion criteria are:

Age ≥ 65 years;Ability to provide informed consent;Able to stand and walk unaided;No acute or untreated medical problems;MoCA ≥22;GDS < 9;SPPB ≥7;Clinical Frailty Scale score between 2 and 4;

For patients with MoCA scores between 22 and 25, an informal caregiver is required to be present during the explanation of the project and the administration of the assessment scales.

The exclusion criteria are:

Failure to meet the inclusion criteria;Use of active implant or non-implant medical devices;Allergy to nickel;Simultaneous participation in other studies;Absence of written informed consent;Occurrence of a myocardial infarction or stroke within the past 6 months;Presence of painful arthritis, spinal stenosis, amputation, painful foot lesions, or neuropathy that significantly limits balance and mobility;Uncontrolled hypertension;Presence of a pacemaker or implantable cardioverter-defibrillator;Advanced Parkinson’s disease or other neuromuscular disorders;Diagnosis of metastatic cancer or undergoing immunosuppressive therapy;Significant visual or hearing impairment.

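### One recruitment MoCA score sets eligibility, strata and outcome baseline, so within-arm MoCA pre/post tests inside the strata would be biased by regression to the mean

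*Protocol article*

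**What the plan says.** - Participants lists the screening thresholds "MoCA ≥22;GDS < 9;SPPB ≥7". Recruitment says when they are applied: "This comprehensive medical examination, conducted before the commencement of the experiment, will determine whether participants meet the inclusion criteria".
- Outcome measures names as a secondary endpoint the improvement in "cognitive status, through Montreal Cognitive Assessment (MoCA"). Table 3 marks MoCA in the R and T2 columns and leaves T0 and T1 empty. SPPB has the same two time points.
- Data collected by the researchers (under Data analysis) plans: "Within each group, independent and dependent variables will be compared between the pre-conditions and post-conditions using the same tests as appropriate".
- The same paragraph assigns the treatment effect to repeated measures ANOVA, "in order to compare the changes over time in the outcome measures between the intervention group and control group", and adds a regression on change adjusted for confounders.
- It then says that, for the analysis of the results, the two kinds of subject are handled separately, "stratified according to the MoCA cutoff (score ≥ 26 for cognitively healthy subjects, score 22 to 25 for subjects with mild cognitive decline").

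No second pre-intervention MoCA is scheduled, and the article does not mention regression to the mean.

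**The concern.** A MoCA score contains measurement error. If people are grouped by their first score and that score is also the starting point for measuring change, its error is carried into the change. On retest the group moves toward the mean of the population it came from, even if nobody has changed.

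The plan contains every ingredient: a stratum defined by the outcome's own baseline, no independent baseline, and a pre/post test. A paired test or a multiplicity correction does not help, because the bias is in the estimated change and not in its standard error.

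At stake is the reading of one secondary endpoint. A rise in the lower stratum of the e-VITA arm could be taken for cognitive benefit, or a fall in the upper stratum for harm, when either may come from the cut-offs alone.

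**Working it through.** **Plan's own figures.** The article states no figure for MoCA change. Its sample size reproduces: for the within-between interaction, λ = f²·N·m/(1−ρ) = 0.11² × 220 × 2/0.5 = 10.65 on 1 and 218 df, which gives power 0.901. With 240 enrolled and 10% dropout, 240 × 0.9 = 216 remain, or 108 per arm.

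**Inputs from the article.** Eligibility at MoCA 22 or more; strata 22–25 and 26 or more; measurement at R and T2; significance level 0.05.

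**Assumptions, not in the article.** Source-population mean μ from 22 to 27, SD 2.5 to 3.5, test-retest reliability r from 0.7 to 0.9, and no treatment, practice or true change.

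**Formula.** For a group selected on its first score, expected change ≈ (1 − r) × (μ − group's mean first score). The 22–25 stratum is a two-sided window, so its mean first score stays between about 23.2 and 24.1 whatever μ is.

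- μ = 26, SD 3, r = 0.8: mean first score 23.82, so 0.2 × (26 − 23.82) = +0.44 (simulated +0.45).
- μ = 23.5: mean first score 23.50, so the change is 0.
- μ = 22, SD 3, r = 0.7: mean first score 23.30, so 0.3 × (22 − 23.30) = −0.39 (simulated −0.40).

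**Simulation.** 2 million subjects per scenario, scores rounded and capped at 30. Mean change at SD 3, for r = 0.7 / 0.8 / 0.9:

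| Source mean | Stratum 22–25 | Stratum 26 or more |
|---|---|---|
| 22 | −0.40 / −0.27 / −0.14 | −1.54 / −1.04 / −0.54 |
| 23.5 | 0 / 0 / 0 | −1.17 / −0.79 / −0.41 |
| 25 | +0.40 / +0.27 / +0.14 | −0.84 / −0.56 / −0.30 |
| 26 | +0.66 / +0.45 / +0.23 | −0.64 / −0.44 / −0.23 |
| 27 | +0.93 / +0.63 / +0.33 | −0.47 / −0.32 / −0.17 |

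With the strata pooled, at means 25 to 26 and SD 2.5 to 3, the drift is small and downward, −0.02 to −0.2.

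**False significance within one arm.** At means 25 to 26 and SD 2.5 to 3, the lower stratum holds 39% to 54% of eligible subjects. That is 108 × 0.39 = 42 to 108 × 0.54 = 58 per arm, leaving about 50 to 66 in the upper stratum. The paired t-test has noncentrality (mean change / SD of change) × √n. Two examples:

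- Lower stratum, μ = 25, SD 3, r = 0.9, n = 55: (0.14/1.37) × √55 = 0.76, so 12% of null trials are significant.
- Upper stratum, μ = 25, SD 3, r = 0.7, n = 53: (−0.84/2.05) × √53 = −2.98, so 83%.

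Over these assumptions the two-sided rate is 12% to about 60% in the lower stratum and 28% to 83% in the upper, against a nominal 5%. At μ = 23.5 the lower stratum returns to 5%.

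**Between-arm check.** In the 22–25 stratum with μ = 26, SD 3, r = 0.8 and 40 per arm, the arms' mean changes differ by about 0.00 and the test on change rejects in 5.0% of null trials.

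**The case against.** The strongest reply is that the plan does not rest its treatment effect on these tests. It assigns that to a between-arm ANOVA, which the drift does not bias because both arms share it in expectation. This stands. The point concerns only a supplementary comparison, and nothing in the article says that a within-arm change will be reported as benefit.

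Second, the article does not state that the pre/post tests will be run inside each stratum. The sentence on separate handling fits a stratified between-arm analysis equally well. This also stands, and it makes the point conditional. But the sentence applies to the analysis of the results generally and follows a paragraph that includes the within-group tests, so the wording does not exclude them either.

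Some stronger readings are tempting but not supported:

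- A reader might infer that subjects with mild decline will appear to improve. The direction depends on the source mean, which is not given. The trial describes its participants as healthy, which makes a mean above 23.5 plausible. Italian recruitment runs through neurology and rehabilitation units, so a lower mean cannot be excluded there.
- A reader might treat SPPB as the same problem. It defines no stratum and has only a one-sided floor (7 or more), which tends to make retest scores fall, not rise. No size was calculated.
- A reader might extend the bias to every outcome inside the MoCA strata. Selection on a noisy MoCA does not by itself bias change in other scales; that would need correlated measurement errors, for which there is no evidence here.
- A reader might add a seasonal shift from the May to December 2023 calendar. It is not regression to the mean, the article gives nothing to size it, and the randomised arms share it.

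**Conclusion.** The concern holds in a limited, conditional form. One MoCA score serves as entry test, stratum label and outcome baseline; that follows directly from the article. If the within-arm pre/post tests are applied to MoCA in the strata, their p-values are not valid under the null, except in the lower stratum when the source mean is near 23.5.

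The upper stratum drifts down in every scenario examined (−0.17 to −1.54 points at SD 3). The lower stratum drifts by −0.40 to +0.93 points over source means 22 to 27 at SD 3. All sizes rest on the assumed mean, SD and reliability. The shifts are small on a 30-point scale, but often large enough for a test to flag them. The uncertain direction does not rescue the test, since a change whose null value may be positive or negative cannot be read as improvement.

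The randomised contrasts, within strata or overall, and the EQ-5D-5L primary analysis are sound on this point.

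**What to change.** In the Data analysis section, under Data collected by the researchers:

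1. Report within-arm MoCA change, overall and by stratum, descriptively and without tests.
2. Base any statement on cognitive improvement on the between-arm difference in T2 MoCA, adjusted for recruitment MoCA as a continuous covariate. Randomisation already removes the bias; the adjustment also deals with chance imbalance in the starting score.
3. Assess whether the effect differs by cognitive level with a treatment-by-baseline-MoCA interaction instead of separate stratum tests.
4. For SPPB, likewise rely on the between-arm contrast.

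The cost is analysis wording only. The recruitment MoCA is already collected, and no visit, participant or measurement is added. The sponsor gives up uncontrolled tests of improvement from baseline within an arm for MoCA.
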